## Abstract

**Background:**

Client discontinuation from outpatient addiction treatment programs is common, and the initial intake is the service delivery point with the highest attrition rate. Replacing the comprehensive intake assessment with a person-centered Motivational Interviewing (MI) intervention is a potential solution to address provider and client concerns about the disengaging, time-intensive nature of the typical initial intake. It remains unclear whether the use of an alternative to the standard intake at the initial visit can fit within typical organizational reporting requirements, whether it decreases attrition, and whether implementation of person-centered intake procedures within outpatient addiction treatment programs is feasible, acceptable, and can be sustained.

**Purpose:**

To describe the methods and design of an effectiveness-implementation hybrid type 1 trial of a Motivational Interviewing at Intake (MII) intervention using the Consolidated Framework for Implementation Research (CFIR).

**Methods:**

The study will determine the effectiveness of two intake conditions: (1) standard comprehensive intake assessment (intake-as-usual [IAU]), and (2) MII consisting of a person-centered discussion between provider and client about the client’s desire and intent to enter treatment. Although both interventions are focused on understanding client presenting complaints and needs for treatment, the delivery differs as the IAU uses a semi-structured assessment guide, while MII applies the theory of MI to have a conversation about treatment engagement. Adults seeking outpatient addiction treatment services will be randomly assigned to the MII condition (n = 75) or the IAU condition (n = 75). Primary outcomes will be client engagement (i.e., treatment entry, attendance, and completion) obtained from the electronic medical record. Secondary outcomes (client motivation and therapeutic alliance) will be putative mechanisms of client engagement assessed immediately before and after the intake. The trial also will explore determinants of effective, sustainable implementation using assessments of organizational readiness and capacity to change, as well as interviews on MII implementation feasibility.

**Conclusion:**

This trial of an MII intervention will investigate the feasibility of a motivational intervention as an initial contact with substance use treatment-seeking clients as well as indicators of intervention effectiveness within the systems where it is employed.

*Trial registration* Clinicaltrials.gov identifier: NCT05489068

## Contributions to the literature

Research demonstrates that the initial intake is the service delivery point when most clients discontinue addiction treatment. For many clients and providers, a client-centered intervention can be more engaging and applicable.Motivational interviewing (MI) is an evidence-based intervention that promotes client engagement and commitment to make choices consistent with personal values and goals, and the client-centered format may also capture intake information required of external agencies.This study will use an effectiveness-implementation hybrid design to examine whether an MI at intake (MII) intervention increases client engagement and to identify the determinants of implementing MII within addiction treatment programs.

## Background

Substance use disorders (SUDs) are prevalent and pervasive chronic problems that can result in myriad personal and societal consequences. In 2020, 40.3 million individuals aged 12 and older (14.5% of the United States population) had an SUD [1], almost twice the number of individuals in 2019 (20.4 million or 7.4%) [2]. Health and social costs associated with SUD exceed $600 billion each year [3]. Although addiction treatment has demonstrable benefits in reducing symptoms and offsetting the costs of SUD, individuals rarely choose to attend formal treatment and then commonly discontinue attending treatment prior to treatment completion, which heightens client risk of returning to harmful substance use and exacerbates treatment facility costs. There are multiple points when a client may disengage from treatment, but 44% of clients do not return after the initial intake [4], making this the service delivery point with the highest attrition rate. Although circumstances beyond the treatment facility likely influence client disengagement [5], understanding which aspects of the initial intake may contribute to client disengagement and developing ways to improve the intake process may help promote client engagement and retention in addiction treatment.

The initial intake session is quite similar across addiction treatment programs, with most outpatient programs (i.e., 93%) [6] tasking a clinical provider with conducting a comprehensive intake assessment to inform treatment planning (“Information-First”). With guidance from the American Society on Addiction Medicine (ASAM), the comprehensive intake assessment asks about the diverse problems individuals experience in relation to their substance use and helps to match clients to their appropriate level of care [7]. Further, the comprehensive intake assessment is an efficient way to gather client information required by health insurance and other funding agencies to determine client eligibility for services. Despite these contributions, clients and providers alike have reported concerns regarding the length, focus, and purpose of the intake assessment, which may contribute to clients not returning to treatment. Specifically, the focus on fact-gathering during intake undermines exploration of the reasons that lead clients to seek treatment in the first place [8]. Relatedly, clients and providers identify the lack of rapport as an impetus for early disengagement [9, 10], precisely because the intake assessment does not address the client’s most relevant concerns. Clients who initiate addiction treatment prefer being included in treatment decisions, working with staff who are empathic, and feeling autonomous in their choices [11–13]. Providers and administrators also are frustrated with an Information-First intake structure, noting that this type of first contact is not engaging, is unacceptably long, and is comprised of excessive, redundant paperwork and questions that are intended largely to meet agency, not client, needs [14–16]. In short, a comprehensive intake assessment does not achieve the primary goal of the initial intake: client engagement.

Given that clients tend to seek treatment when their lives have become unmanageable, it is critical to explore why the client wants treatment *now* during their initial contact with a treatment agency. Despite empirical support for a patient-oriented, recovery-based model of care [17–19], addiction treatment programs have made few, if any, changes to their intake services. The primary source of tension may be that most programs are beholden to state/federal agencies and health insurance companies, all of which require a wealth of client information at the outset to provide financial support or reimbursement [20]. Unfortunately, most agencies are not able to offer a broad variety of treatments suitable to the problems that are carefully identified during this intensive intake process. Further, referral sources also are usually limited, resulting in a detailed assessment of problems that cannot be readily addressed.

Previous research focused on adapting intake procedures to focus more on client engagement in addiction treatment programs has tested the value of adding Motivational Interviewing (MI) to the intake assessment. These interventions are often referred to as “incorporating” or “integrating” MI. The result has often been a null effect on client engagement and retention [21–26]. One reason may be how MI was implemented into the intake process. Specifically, some researchers provided a comprehensive assessment *prior* to delivering MI whereas others delivered a comprehensive assessment *within* an MI framework; both methods led to inconsistent client engagement outcomes. No prior work has tested the impact on client engagement rates as a *replacement* to the comprehensive assessment. Another reason for the inconsistency may be the variable format of the MI interventions. Studies either integrated components from other evidence-based interventions into the MI intervention (e.g., personalized normative feedback [27]) or they included fact-gathering questions in the MI intervention [28]. Adding non-MI components to an MI intervention precludes identifying what aspects of the intervention led to the mixed findings so commonly seen in the MI literature [29]. This is an important limitation that is likely due to the rapid, widespread dissemination of MI [30], with minimal attention to its effective, sustainable implementation into standard practice.

It may be important to change the entire intake process, rather than build in MI to the currently implemented lengthy intake process. Changing the intake process for addiction treatment may also require broader changes in programs, further complicating the adoption potential of a new intake approach. For example, the workflow may change such that more paperwork may be required either before or after intake rather than during the intake when the provider is attending carefully to the client. Modifying the Information-First approach also requires re-training personnel, which may be difficult to initiate and sustain. Prior to adapting intake procedures, it is critical to first determine the effectiveness and feasibility of replacing existing intake procedures with an alternative intake process. With an evidence base, findings could be used to encourage external agencies to modify their requirements of an agency’s first contact with clients.

The current trial will utilize an effectiveness-implementation hybrid type 1 (HEI-1) design to evaluate the clinical effectiveness of a Motivational Interviewing at Intake (MII) intervention to increase client engagement, retention, and success in treatment, as well as two theoretical mechanisms of engagement (client motivation and therapeutic alliance). Simultaneously, the trial will examine perceptions among personnel of facilitators and barriers to the effective and sustained implementation of the MII intervention. Given that clients and providers alike recommend improving an intake appointment in a manner that fosters therapeutic rapport and encourages client engagement, MI may be optimal, with demonstrated evidence to increase client engagement and commitment to make behavioral changes [31]. In contrast to prior efforts to integrate MI into standard intake assessment, this trial will test whether *entirely replacing the standard intake assessment with an MII intervention* can promote client engagement. An evaluation of the feasibility of implementing the intervention in standard practice will guide recommendations for addressing reporting requirements while also assuring the primary goal of engaging clients in treatment at the first contact.

### Study aims

The primary aim of this trial is to determine the clinical effectiveness of MII intervention compared to intake-as-usual (IAU) on outcome variables of client entry, treatment attendance, and completion of an outpatient addiction treatment program. Two mechanisms of client engagement will be examined—changes in client motivation and client perception of the therapeutic alliance. The secondary aim of this trial is to determine the feasibility of implementing a motivational intervention across outpatient addiction treatment programs, based on quantitative and qualitative feedback from addiction treatment personnel. The Consolidated Framework for Implementation Research (CFIR) [32] will guide the approach of the implementation aim with a goal of identifying determinants of effective, sustained implementation of MII across the five broad CFIR domains: intervention characteristics, outer setting, inner setting, characteristics of individuals involved, and implementation process. Personnel will complete quantitative measures of organizational readiness and capability to change the intake process before and after the clinical trial ends, as well as a CFIR-guided individual interview after the clinical trial ends to identify specific facilitators and barriers to implementing the MII intervention into standard practice.

## Methods

### Study design

Funded by the National Institute on Drug Abuse (NIDA) as part of an initiative to improve behavioral healthcare services, the MII trial uses an HEI-1 design, where the primary outcome is clinical effectiveness, and the secondary outcome is implementation feasibility [33]. The study will be sufficiently powered to detect our primary outcome, which is the impact of the intervention on client entry in the outpatient treatment program, as well as the number of treatment sessions attended and whether client participants completed the three-month program (our secondary outcomes).

To determine clinical effectiveness, a single-blind randomized clinical trial (RCT) will be used at two community-based addiction treatment programs—one that provides in-person services and one that provides telehealth services. Eligible clients will be those scheduled for an initial intake to the outpatient programs at each site. Interested participants will be randomly assigned to receive MII or intake-as-usual (IAU) by the on-site, clinical intake providers (see Fig. 1, CONSORT diagram). To determine implementation feasibility, a mixed-methods pre-post design will be used to evaluate changes in readiness and capability to change the intake process among addiction treatment personnel at both clinical sites. Specifically, we will administer a survey comprising several measures of implementation determinants to personnel before and immediately following the RCT, as well as an individual interview after the RCT to identify key facilitators and barriers to implementation effectiveness. To understand the feasibility of changing the intake process across addiction treatment programs, we also will administer the survey and individual interview to addiction treatment personnel employed at other substance treatment programs in New Mexico (see Fig. 2 for client and personnel study procedures).

**Fig. 1 Fig1:**
[figure not shown]
Clinical effectiveness trial diagram

**Fig. 2 Fig2:**
[figure not shown]
Client and personnel participant study timelines

The treatment protocol was approved by the University of New Mexico Institutional Review Board and is registered on ClinicalTrials.gov (NCT05489068). Electronic consent is required for personnel participation, and informed consent is required for client participation in the study.

### Study setting

The MII trial is being conducted in two community-based addiction treatment programs, one based in New Mexico and the other based in California. These sites provide outpatient treatment services to adults with SUD. An email detailing the MII trial and requesting participation as a study site was sent to 25 eligible addiction treatment facilities. Five facilities agreed to allow staff to be contacted by researchers for the implementation portion of the trial. However, three of the facilities were unable to recruit clients for the randomized clinical trial due to competing demands (e.g., implementing changes to other treatment services). The two participating treatment facilities are community-based addiction treatment programs that have similar intake procedures for clients seeking outpatient services, though one site provides in-person services and the other provides telehealth services.

### Study participants: recruitment, eligibility, randomization, and blinding

Client participants will be recruited from among individuals scheduled for a standard intake for the outpatient program (OP) at either of the two study sites. As part of standard procedures at both study sites, clients contact the treatment facility and complete a brief phone screener to identify their presenting concerns (i.e., substance use and mental health issues) and determine their level of care (e.g., detoxification services, OP), and are then scheduled for the intake appointment. Across both facilities, the intake appointment for clients seeking OP is the same. Clients who are scheduled for an OP intake will be recruited for study participation upon arrival to their scheduled intake appointment. Clients will be deemed eligible if they are at least 18 years old and English-speaking. Clients will be excluded from participation if they are experiencing severe withdrawal symptoms or are experiencing current symptoms of psychosis, mania, or suicidal intent. Exclusion criteria are determined through standard enrollment procedures at each site, such that clients first meet with administrative staff to complete consent for treatment paperwork and answer questions about their current need for detoxification services.

A research assistant will meet with eligible and interested participants to review the consent form, answer any questions, and assure the client that participation is not a requisite for concomitant care. Consenting client participants will be randomized to MII or IAU and randomization will be stratified by gender. The randomization sequences will be implemented (and concealed) in Redcap, a secure, customizable clinical trials management system used for data management and performed by a member of the research team who will not be involved in data collection and analytic procedures. Therefore, the principal investigator, research staff who will be conducting the informed consent and assessments, and all co-investigators will be masked to the intervention assignment. Only the designated project manager, one research assistant not involved in assessments or analyses, and the study intake therapists will not be masked to condition.

Addiction treatment personnel also will be included as participants to evaluate implementation feasibility. Personnel participants will comprise two groups: study-involved and study-naïve personnel. Study-involved personnel will be eligible to participate if they are English-speaking adults currently employed at one of the two study sites. Study-naive personnel will be eligible to participate if they are English-speaking adults who are currently employed at an addiction treatment program in the state of New Mexico. Study-involved personnel will be recruited from the two study sites but excluded from participation if they currently hold a leadership position (i.e., owner or clinical director). Study-naïve personnel will be recruited via email from treatment agency directors across the state of New Mexico and excluded if their job responsibilities include providing medical or administrative services. No manipulation or randomization procedures are in place for personnel participants. Whereas study-involved personnel participants will be asked to complete all implementation procedures, including pre-MII training assessments, optional MII training, and post-trial assessments and interview, the study-naïve personnel will be asked to complete only post-trial implementation procedures (i.e., post-trial assessments and interview).

### Sample size and power analysis

An intent to treat approach will be employed such that participant data will be analyzed based on the randomization assignment status, regardless of levels of engagement in the treatment program. Target enrollment of client participants is 150, with approximately 75 in the MII condition and 75 in the IAU condition. Power analyses based on a meta-analysis of 42 studies that evaluated client engagement following an MI intervention suggest that 75 participants per condition will provide sufficient power (0.80) to detect a medium effect size (*d* = 0.24 [CI 0.17, 0.31]) [34]. Given that client participant consent, baseline, follow-up assessments, and assigned intake condition will occur within a single visit, and that primary outcomes are based on electronic medical record review, we did not account for potential attrition.

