### Outcomes

Clinical effectiveness is prioritized in the current study, and implementation feasibility is a secondary outcome. As such, the primary effectiveness outcome is whether clients enter the outpatient treatment program (i.e., attend their first scheduled treatment session). Secondary effectiveness outcomes include the number of treatment sessions attended and whether clients completed the outpatient treatment program. All effectiveness outcomes will be assessed using electronic medical record data and putative mechanisms of engagement will be assessed using self-report measures administered before and after the assigned intake condition. Mechanisms of effectiveness include change in client motivation and therapeutic alliance.

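### 75 clients per arm, power 0.80 and d = 0.24 cannot all hold: at an assumed two-sided 5% level, power at d = 0.24 is about 0.31

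*Protocol article*

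**What the plan says.** The Sample size and power analysis section sets the size: "Target enrollment of client participants is 150, with approximately 75 in the MII condition and 75 in the IAU condition". It then says that power analyses based on a meta-analysis of 42 studies of engagement after an MI intervention "suggest that 75 participants per condition will provide sufficient power (0.80) to detect a medium effect size". The effect is given in the same sentence: "to detect a medium effect size (*d* = 0.24 [CI 0.17, 0.31". There is no allowance for dropout ("we did not account for potential attrition"), because the primary outcomes come from the medical record.

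The Study design section repeats the conclusion: "The study will be sufficiently powered to detect our primary outcome". The Outcomes section makes that outcome binary: "the primary effectiveness outcome is whether clients enter the outpatient treatment program". The Statistical analyses section compares the arms on it by logistic regression with covariates.

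The power paragraph gives no significance level, sidedness or control-arm entry rate. The only figure in the article that bears on a control rate is a cited one in the Background: "44% of clients do not return after the initial intake".

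**The concern.** A standardised difference of 0.24 lies close to the conventional small effect (0.2) and well below the conventional medium one (0.5). A two-arm comparison with 75 per arm does not normally have 80% power for so small a difference, so the sentence needed checking.

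The stated power governs how a null result will be read. The Background says that earlier attempts to add MI to intake often found no effect, and the Discussion makes a larger multisite trial depend on promising results. If the expected effect is d = 0.24 and the real power is about 0.31, the trial would miss it about 69% of the time (1 − 0.31). Readers told that power was 0.80 could take a non-significant result as evidence that MII does not help.

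**Working it through.** **Inputs from the article.** n = 75 per arm, 1:1; d = 0.24, CI 0.17 to 0.31; stated power 0.80; no dropout inflation.

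**Assumptions.** Two-sided alpha 0.05, with other levels tried below. For the binary outcome, control entry of 56% (100% − 44%, the Background figure), with 30% to 80% also tried.

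**1. Attempt to reproduce 0.80.** Normal approximation: power = Φ(d·√(n/2) − 1.96).
- d·√(n/2) = 0.24 × √37.5 = 1.470
- Power = Φ(1.470 − 1.960) = Φ(−0.490) = 0.312; the exact t-test gives 0.309.

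The stated 0.80 is not reproduced. Over the quoted interval (t-test):

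| d | power, two-sided 0.05 |
|---|---|
| 0.17 | 0.18 |
| 0.24 | 0.31 |
| 0.31 | 0.47 |

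**2. Size needed, and effect detectable.**
- n per arm for 80% at d = 0.24: 2 × (1.960 + 0.842)² / 0.24² = 273 (274 with the t-test), or 2 × 274 = 548 in total against 150 planned.
- Detectable d at 75 per arm: (1.960 + 0.842) × √(2/75) = 0.457 (0.460 with the t-test).
- At d = 0.5, 75 per arm gives power of about 0.86.

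**3. Could an unstated input explain 0.80?** At d = 0.24:
- One-sided 0.05: 0.43. One-sided 0.10: 0.57. One-sided 0.20: 0.74.
- Reading 75 as 150 per arm: 0.55. A paired test with 75 pairs: 0.54.
- Covariate adjustment would need an R² of about 0.73.
- Only readings that do not fit this design come near: 0.24 taken as Cohen's f (0.84), as a correlation with N = 150 (0.84), or as a one-sample test with N = 150 (0.83).

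**4. The binary primary outcome.** Logistic conversion: ln(OR) = d·π/√3.
- OR = exp(0.24 × 1.814) = 1.545
- Control odds 0.56/0.44 = 1.273; MII odds 1.273 × 1.545 = 1.967; MII entry 66.3%
- Difference 0.103; pooled SE 0.0796; unpooled SE 0.0792
- Power = Φ((0.103 − 1.960 × 0.0796)/0.0792) = Φ(−0.67) = 0.25; 80% would need 351 per arm.

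On this conversion, power is 0.24 to 0.26 for control rates of 30% to 60%, 0.21 at 70% and 0.17 at 80%. If 0.24 is read as Cohen's h, power is about 0.31 throughout.

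**5. What 75 per arm offers on the entry scale.** From 56% in IAU, 80% power is reached at about 77.4% in MII.
- OR = (0.774/0.226)/(0.56/0.44) = 2.69
- This contrast is about 0.46 as Cohen's h, but ln(2.69) × √3/π = 0.55 on the logistic scale.
- 95% CI half-width for the entry difference: 1.96 × √((0.2464 + 0.2234)/75) = 0.155 at 56% versus 66.3%, and about 0.147 at 56% versus 77.4%.

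**The case against.** The best defence is that the 0.80 may be right and the bracketed effect misplaced. The sentence says medium, and 75 per arm has about 86% power at the conventional medium value of 0.5 and 80% at about 0.46. The sample may have been set for such an effect, with the meta-analytic estimate then entered beside it. This stands as a possible explanation, and the article cannot settle it. It does not rescue the sentence, which attaches 0.80 to 0.24.

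The missing alpha is also fairly raised: an article may leave it to the full protocol, and its absence is not a fault here. But a one-sided 5% test gives only 0.43, and even one-sided 20% gives 0.74.

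Some stronger readings are tempting, and the documents do not support them:
- *That power for treatment entry is 25%.* This rests on a 56% control rate, which comes from a cited background figure never adopted as a design input for these two sites, and on one choice of conversion. Only the range of about 0.17 to 0.31 can be defended.
- *That a standardised difference is the wrong metric for a binary outcome.* A meta-analysis can express binary engagement outcomes as d, and the conversion may be in the full protocol.
- *That therapist clustering lowers power further.* The article gives no intraclass correlation and no number of therapists, so no size can be put on this.

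**Conclusion.** The power statement is wrong as written. With 75 per arm and an assumed two-sided alpha of 0.05, power at d = 0.24 is about 0.31, not 0.80. It is 0.43 one-sided, and 0.47 at the top of the quoted interval. About 274 per arm would be needed at d = 0.24; 75 per arm has 80% power at d of about 0.46, nearly twice the quoted effect. Calling 0.24 medium conflicts with the usual convention.

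For treatment entry, power at d = 0.24 is about 0.25 under the 56% and logistic assumptions, and about 0.17 to 0.31 across the alternatives tried. The adequacy claim under Study design therefore does not hold at the effect the article cites.

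A reader might infer that the sample size itself is the mistake and that the trial must grow to about 548. The documents do not support that step. They show that the three figures disagree, not which one is in error, and a trial of 150 can be reported honestly with its real detectable effect.

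**What to change.** Keep 150 clients and restate the power paragraph, for example:

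> *With 75 per arm and two-sided alpha 0.05, power at the meta-analytic d = 0.24 is about 0.31; 80% power is available for a standardised difference of about 0.46. For treatment entry, assuming 56% in IAU, 80% power is available for about 77% in MII (odds ratio about 2.7).*

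In addition:
- Do not equate 56% versus 77% with d = 0.46 unless the scale is named: about 0.46 as Cohen's h, about 0.55 on the logistic scale.
- Stop describing d = 0.24 as medium. If the sponsor's records show that a larger effect was intended, state that effect and its basis separately from the meta-analytic estimate.
- Qualify the sufficiency claim under Study design to match.
- State that the primary result will be interpreted from the estimate and its 95% confidence interval, expected to be about ±15 to 16 percentage points for the entry difference, and that a non-significant result is not evidence of no effect.

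The cost is rewording in two sections and a less favourable stated power. No clients are added.
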